### Sites and sites monitoring

The study will be conducted at up to twenty sites within Italy. Three site visits for each center will be performed (start of enrollment, mid-study, end of enrollment). Additional site visits will be performed as required. The coordinating center (University of Bologna – Policlinico S.Orsola-Malpighi) will supervise all aspects of the study and will be available to participant sites 24 hours, 7 days. All sites must have significant experience in treating AECOPD and with ECCO_2_R (i.e., all centers must routinely use continuous renal replacement therapy and perform at least 10 ECCO_2_R runs per year). Frequent investigators’ meeting will be planned in order to motivate enrollment. The coordinating center will provide logistic support to all participating sites in order to ensure efficient enrolment.

More specific data about sites can be obtained from the corresponding author.

### Data and data monitoring

The study will be conducted in accordance with the current approved protocol. Independent study monitors will verify that the clinical trial is conducted, and data are generated, documented and reported according to the protocol and the current national and international regulations. Data quality will be assessed by the independent study monitors and frequent site visits (at least 3 visit/site/year) will be performed at each site, in order to ensure consistency throughout the duration of the trial.

### Access to data and publication

All data will remain property of the researchers and direct access to data will be granted only to authorized representatives of the regulatory authorities for inspective purposes.

Trial results will be communicated to relevant groups (participants, healthcare professionals, the public) via publication into peer-reviewed journal(s).

### Statistical analysis

Statistical analysis will be conducted according to the intention to treat principles (ITT), analyzing the whole sample size of all randomized patients.

Secondary analyses will be performed according to protocol adherence on “as treated” populations, with explorative and/or explicative purposes only.

No interim analyses will be performed. No predefined subgroup analysis will be performed.

#### Baseline characteristics

The baseline characteristics of the patients will be described by group, using the most appropriate statistics: quantitative variables will typically be summarized using frequencies and percentages for appropriate categorizations and may also be summarized using descriptive statistics. For variables summarized with descriptive statistics, the following will be presented: N, mean, standard deviation, median, q1, and q3. Categorical variables will be presented using frequencies and percentages.

No statistical comparisons between groups will be done on baseline variables.

#### Evaluation of the primary endpoint

EFS will be estimated using the Kaplan-Meier estimator applied to the ITT population, and compared between those who received NIV plus ECCO2R and those who did receive only NIV using the stratified log-rank test.

In addition, the Hazard Ratio (HR), along with 95% confidence intervals, will be estimated from a stratified Cox model with treatment group as a covariate.

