### Inclusion criteria

Patients older than 18 and younger than 90 yearsDocumented clinical history of COPDICU admission for exacerbation of COPD requiring NIV support

After two hours of NIV at least two of the following criteria for high risk of NIV-failure [14, 22] must be fulfilled:
arterial pH ≤ 7.25respiratory rate ≥30 breaths/minuse of accessory muscles or paradoxical abdominal movements

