##### Randomization

Central randomization by blocks stratified only by center. The randomization is centralized: a random sequence stratified by center will be generated in order to guarantee a balancing of the arms within the center; the sequence will be implemented following a block algorithm. The random sequence will be generated by a server run by the coordinating center. Participant sites will obtain the allocation of each enrolled patient upon enrolment, after checking for inclusion/exclusion criteria.

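### The primary analysis uses no patient-level baseline covariate: it is valid, but it gives up efficiency of unknown size in a trial expecting about 150 events

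*Protocol article*

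**What the plan says.** In the protocol article, the section on evaluation of the primary endpoint compares the arms "using the stratified log-rank test". It then takes the hazard ratio from a "stratified Cox model with treatment group as a covariate". The log-rank test is therefore the primary comparison, and the Cox model supplies the estimate beside it. The strata are not named there. They are presumably the centres, because the Randomization section says "Central randomization by blocks stratified only by center", and the section on sites says "The study will be conducted at up to twenty sites within Italy".

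For entry, the Inclusion criteria set an age range and require this: "After two hours of NIV at least two of the following criteria for high risk of NIV-failure". The three criteria are arterial pH, respiratory rate, and accessory-muscle use or paradoxical abdominal movement. Sites obtain the allocation "upon enrolment, after checking for inclusion/exclusion criteria", so eligibility is settled before the arm is known.

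For secondary endpoints, the article plans adjusted hazard ratios from a Fine and Gray model without naming the covariates.

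**The concern.** Patient-level prognostic information plays no part in the randomisation, the primary test or the primary estimate. Yet some of the values that define a patient's risk at entry are in hand before allocation. When such values do predict the outcome, a test that conditions on them has more power than one that ignores them, at no cost in patients or measurements. This matters more here than usual, because the 28-day endpoint yields far fewer events than the stated power needs. The article also says that recruitment had not begun, so covariates could still be chosen without sight of outcome data.

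**Working it through.** **1. Inputs.** From the Sample size section: 284 patients (142 per arm), two-sided alpha 0.05, 90% power, hazard ratio 0.67, control event-free survival 40%, 24 months of accrual plus 1 month of follow-up, no dropout. From the Primary outcome section: the endpoint is assessed at day 28.

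**2. Reproducing the plan's figure.** Events needed for 90% power:
- Schoenfeld: 4(1.96 + 1.2816)² / (ln 0.67)² = 42.03 / 0.1604, giving 263.
- Freedman: (1.96 + 1.2816)² × (1.67/0.33)² = 10.51 × 25.61, giving 270.

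Suppose every patient is followed to month 25. With monthly hazards λ = −ln 0.40 = 0.916 (control) and 0.67 × 0.916 = 0.614 (treatment), the event probability is 1 − [exp(−λ) − exp(−25λ)]/(24λ). This gives 0.982 and 0.963, mean 0.973. The total is then 263/0.973 ≈ 270 to 270/0.973 ≈ 278, close to 284, and power at 284 is 90.7 to 91.4%. So the stated figure is reproduced only if patients keep contributing events to the end of the study.

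**3. The endpoint as defined, 28 days per patient.** Treatment event-free survival is 0.40^0.67 = 0.541, so the event probabilities are 0.600 and 0.459. Events: 142 × (0.600 + 0.459) ≈ 150.
- Schoenfeld power: Φ(√150.3 × 0.4005/2 − 1.96) = Φ(0.495) = 69%.
- Freedman power: Φ(√150.3 × 0.33/1.67 − 1.96) = Φ(0.463) = 68%.

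For 90% power, about 263/0.529 = 497 to 270/0.529 = 510 patients would be needed.

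**4. Which values exist before allocation.**
- Age is an entry criterion for everyone.
- Arterial pH need not be one of the two risk criteria met. However, the exclusion on PaO₂/FiO₂ calls for an arterial blood gas, which should also yield pH.
- Respiratory rate need not be one of the two criteria met either. It is hard to imagine it unrecorded in an ICU patient on NIV, but the article does not say so outright.

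**5. What adjustment would change.** Simulation of 284 patients, 3,000 trials per setting (Monte Carlo standard error about 0.8 points), with exponential times censored at day 28 and marginal event-free survival held at 40% and 54.1%. Assumptions not in the documents: 20 equally likely centres, blocks of 4, centre SD 0.2 on the log hazard, and three independent baseline covariates whose combined score has the SD shown.

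| SD of score (log hazard) | Stratified log-rank, as planned | Stratified Cox, three covariates | Gain (points) | Conditional hazard ratio |
|---|---|---|---|---|
| 0 | 67.5% | 67.2% | −0.3 | 0.666 |
| 0.3 | 69.1% | 70.2% | 1.1 | 0.657 |
| 0.5 | 68.9% | 74.0% | 5.1 | 0.641 |
| 0.8 | 72.5% | 84.5% | 12.0 | 0.606 |
| 1.0 | 71.3% | 88.0% | 16.7 | 0.578 |

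Only day-28 survival is held fixed across rows, so the power of the planned test is not constant. A separate simulation with two covariates (1,500 trials per setting) gave the same pattern. Power went from 67.3 to 68.2% with no prognostic value, and from 67.6 to 70.3%, 68.2 to 75.3% and 67.3 to 81.5% at hazard ratios of 1.25, 1.5 and 1.75 per SD. Its type I error stayed near 5% (800 null trials).

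**The case against.** The strongest reply is that nothing here is wrong. A stratified log-rank test fits centre-stratified randomisation, it is the kind of test on which the sample size rests, and it is valid without covariates. That stands: this is a matter of efficiency.

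A second reply is that covariates belong in the analysis plan, which is not shown. This carries less weight, because the article does not leave the primary model open. It states the test and names treatment as the covariate.

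A third reply is that the benefit is unproven, and this also stands. The article presents pH and respiratory rate as markers of NIV failure, not of the five-part composite. Entry at pH ≤ 7.25 or a rate ≥ 30 can narrow their spread and weaken them as predictors.

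Four stronger readings are tempting, and the documents do not support them:
- That the Cox model gives away the power. The log-rank test sets the power of the primary comparison, so adding covariates to the Cox model alone would change nothing there.
- That the inclusion criteria force all three values to be recorded in every patient. Two of three risk criteria suffice, so only age follows from that section alone.
- That the unadjusted hazard ratio is biased towards 1. Marginal and conditional hazard ratios are different quantities, and the planned 0.67 matches the marginal 40% versus 54%.
- That adjustment would restore 90% power. The centre-stratified adjusted model did not reach it in any setting simulated.

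**Conclusion.** The point holds as a recommendation on efficiency. The primary analysis is valid but ignores entry values that should be available for essentially every patient. Against a baseline of about 68 to 69% power, adjustment would add from nil to roughly 5 points if the prognostic score has an SD of up to 0.5 on the log-hazard scale, and more if it is stronger. That strength is an assumption throughout, since no section of the article supplies it. The downside in power is negligible: with uninformative covariates the two tests agreed to within Monte Carlo error. The shortfall of about 150 events against 263 to 270 is a separate defect of the sample-size statement. It makes efficiency worth having, but adjustment does not cure it.

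**What to change.** Before recruitment, amend the section on evaluation of the primary endpoint so that:

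- the primary treatment test and hazard ratio come from a Cox model stratified by centre (named as the stratum), with treatment plus age, respiratory rate and arterial pH as continuous terms;
- respiratory rate and pH are defined as values taken before randomisation;
- a simple rule covers any missing baseline value, for example single imputation without regard to arm;
- the stratified log-rank test and the unadjusted stratified hazard ratio are reported as supportive.

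The test has to move with the estimate, or no power is gained. The cost is more than a change of wording in one respect: the primary test would no longer be the log-rank on which the trial was sized, and this should be stated openly. The adjusted hazard ratio is also conditional. In the simulation, the same marginal 40% versus 54% corresponded to a conditional hazard ratio of 0.641 at SD 0.5, so both figures should be shown side by side. No extra patients are needed and, provided that the three values are captured on the case report form, no extra measurements. The sample-size statement needs its own correction.

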#### Evaluation of secondary endpoints

All components of the primary composite endpoint (singleton) will be examinated separately as independent proportion. The cumulative incidence of sepsis, hypercapnic respiratory failure, hypoxemic respiratory failure, prolonged mechanical ventilation >28days, tracheostomy and endotracheal intubation will be estimated with the Gooley method, to take into account the competitive risk of death, and compared with the Grey test. The Fine and Grey model will be used to estimate adjusted HR and their 95% CI. In addition, overall survival (OS) will be analyzed with Kaplan-Meier method and compared with the log rank test. A Cox proportional hazard model (if appropriate) will be used to estimate the Hazard Ratios (HR) and the 95% CI.Hospital length of stay and ICU length of stay will be described in each arm as median and interquartile range; they will be compared with the Wilcoxon rank sum test. The 95% confidence interval (CI) of the mean difference of measure will be estimated with a bootstrap method.Hospital mortality will be expressed as rate and a Chi square test will be used to evaluate the difference between the two groups.Incidence of adverse events and severe adverse events will be expressed as rate and a Chi square test will be used to evaluate the difference between the two groups.

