### Safety

Safety will be assessed by measuring the frequency of serious adverse events (SAE). A serious adverse event (SAE) in the trial is defined as:
any event that is fatal or immediately life threatening, permanently disabling, severely incapacitating or requires prolonged hospitalization **OR**any event that may jeopardize the patient and requires medical or surgical intervention to prevent one of the outcomes listed above **AND**which the attending physician perceives may be directly related to enrollment in the clinical trial.

Investigators will report severe adverse events to the clinical coordinator. An independent Data and Safety Monitoring Board (DSMB) will receive a detailed written report and evaluate whether the SAE is attributable to ECCO_2_R. SAE will be considered to be study-related if the event follows a reasonable sequence from a study procedure and could be produced by the study procedure. SAE will be considered not study related if they are thought to be primarily related to the underlying disease and its sequelae.

Other adverse events not fulfilling the above definition are recorded as ECCO_2_R related adverse events (ECCO_2_R-AE) and classified as:

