**mechanical**
difficulties upon catheter insertion (i.e. need for >2 attempts at catheter insertion during primary placement procedure);pump malfunction (i.e. need for >2 consecutive interventions during the same treatment with the same blood circuit, regardless of the need for stopping the procedure or for replacement of the pump);membrane lung clotting (leading to interruption of ECCO_2_R and/or circuit replacement);catheter displacement;cannula thrombosis;air in the circuit;tubing rupture;system leaks;**clinical**:
hemolysis (i.e. serum free hemoglobin ≥ 100 mg/L or hematocrit reduction not related to hemorrhage or other causes of blood loss, jaundice, hemoglobinuria, impaired renal function);bleeding (related to cannula insertion, and/or at cannula site; bleeding is considered “significant” if requires administration of ≥1 unit of packed red cells);hemodynamic instability (see criteria in the ‘Treatment of participants’ paragraph);ischemic/gangrenous bowel;pneumothorax;renal complications (i.e., occurrence of serum creatinine >1.5 mg/dl after initiation of ECCO_2_R);infectious complications (i.e., occurrence of culture-proven new infection after initiation of ECCO_2_R);thromboembolic complications (i.e., occurrence of deep venous thrombosis or pulmonary embolism after initiation of ECCO_2_R);thrombocytopenia (platelet count below 50,000/mm^3^);hypofibrinogenemia (i.e. fibrinogen < 1.5 g/L);neurologic complications (i.e. occurrence of cerebral infarction, or clinical seizure, or cerebral hemorrhage or cerebral edema after initiation of ECCO_2_R).

Each SAE will be notified by the investigator to the coordinating center, DSMB and ethics committee within 24 hours of occurrence. A detailed report will be sent by the investigator within 5 days of occurrence. The DSMB will examine every report immediately and will take every measure needed to ensure patients safety. Moreover, the DSMB will also meet every 30 enrolled patients to perform all necessary safety analyses. The DSMB can irrevocably halt the trial if the data analysis would show risks for patients’ safety.

An appropriate insurance policy, covering all enrolled patients for possible harm will be activated before enrollment of the first patient.

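### The between-arm chi-square on adverse events uses a class in which 13 of 19 listed items cannot occur in the control arm, and the SAE definition leaves the role of relatedness open

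*Protocol article*

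**What the plan says.** All references are to the Protocol article.

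- **Secondary outcomes** lists the incidence of adverse events and takes the definition from the Safety section.
- **Safety** defines an SAE by two limbs joined by OR: an event with a serious consequence, or an event needing intervention to prevent one. It then adds, after AND, the condition "which the attending physician perceives may be directly related to enrollment in the clinical trial".
- **Safety** continues: "Other adverse events not fulfilling the above definition are recorded as ECCO_2_R related adverse events". It defines no other class of non-serious event.
- **The list that follows** has 8 mechanical and 11 clinical items. Some clinical items depend on the device having been started, such as "occurrence of culture-proven new infection after initiation of ECCO_2_R" and "occurrence of serum creatinine >1.5 mg/dl after initiation of ECCO_2_R". Bleeding is limited to the catheter: "bleeding (related to cannula insertion, and/or at cannula site". Others carry no such condition, such as "thrombocytopenia (platelet count below 50,000/mm^3".
- **Evaluation of secondary endpoints** then plans: "Incidence of adverse events and severe adverse events will be expressed as rate and a Chi square test will be used to evaluate" how the two groups differ.
- **Trial design** states that the trial is unblinded. **Sample size** gives 142 patients per arm and assumes no crossover.

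**The concern.** A comparison between randomized arms is a fair measure of harm only if an event can be counted in either arm on the same terms. Here the definition, the outcome and the test are all fixed in the article, and they do not fit together. Most of the listed items presuppose the device, and the class as a whole is labelled as related to it.

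The Abstract and Discussion frame the trial as weighing the risks of invasive ventilation against the complications of ECCO2R. New infection, kidney injury and thromboembolism can arise in ventilated controls too. If they are counted only after ECCO2R has begun, equal risks will look like excess harm from the device. The DSMB meets every 30 enrolled patients and can halt the trial. If it uses the same definitions, it has the same deficient comparator.

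**Working it through.** The article gives no figure for this comparison, so there is none to reproduce. The check is an item count, a calculation of scale, and a reading of the SAE definition.

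**1. Which items can be counted in Group A?** (Safety section; no crossover, as Sample size assumes)

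| Items | Number | Possible in Group A? |
|---|---|---|
| Mechanical (catheter insertion, pump, membrane lung, displacement, cannula thrombosis, air, tubing, leaks) | 8 | No, they need the device |
| Renal, infectious, thromboembolic, neurologic | 4 | No, onset must follow the start of ECCO2R |
| Bleeding | 1 | No, limited to the cannula |
| Hemolysis, hemodynamic instability, ischemic bowel, pneumothorax, thrombocytopenia, hypofibrinogenemia | 6 | Yes by their own wording, but they sit under the ECCO2R-related heading |

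8 + 4 + 1 = 13 of 19 are impossible in Group A. Capture of the other 6 in Group A is not settled by the text.

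**2. Where is the difference an artefact?** The mechanical and cannula events are a real added burden of the device, and their absence in Group A is genuine. The artefact lies in the four items tied to the start of ECCO2R. Bleeding away from the cannula joins them wherever sites log it under the bleeding item for Group B. Read literally, that item omits such bleeding in both arms.

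**3. Size for one item.** With n = 142 per arm, N = 284, 0 events in Group A and x in Group B, the uncorrected Pearson statistic reduces to X² = N·x/(N − x).

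- Assume a true infection risk of 10% in both arms. Expected in Group B: 0.10 × 142 ≈ 14. Recorded in Group A: 0. X² = 284 × 14/270 = 14.73, so z = 3.84 and p is about 0.0001, for a true difference of zero.
- Smallest count reaching 0.05: x = 3 gives 284 × 3/281 = 3.03 (p = 0.082); x = 4 gives 284 × 4/280 = 4.06 (p = 0.044).
- With continuity correction or Fisher's exact test, 6/142 is needed (p = 0.039 and p = 0.030).

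**4. Does this depend on the assumed 10%?** The next table gives the exact binomial probability that the uncorrected chi-square rejects at two-sided 0.05 when both arms have the same true risk. Columns show the share of Group A events that is counted. Risks and shares are assumptions. The 0.05 level is also assumed, since the article states it only for the primary test.

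| True risk, both arms | 0% counted | 25% counted | 50% counted | All counted |
|---|---|---|---|---|
| 2% | 32% | 17% | 9% | 4.5% |
| 5% | 93% | 43% | 18% | 4.8% |
| 10% | about 100% | 77% | 35% | 4.9% |
| 20% | about 100% | 98% | 67% | 5.0% |

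With equal capture the test holds its level. The fault is in the definitions, not in the chi-square.

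**5. The SAE definition, read both ways.**

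- *AND binds only the second limb.* Fatal, life-threatening, disabling or hospitalization-prolonging events count in both arms whatever their cause. Group A is then far from zero.
- *AND binds both limbs.* Every SAE depends on a physician who knows the arm judging a relation to enrolment. A serious event judged unrelated fails the SAE definition and, by the next rule in Safety, falls into the ECCO2R-related class, even in a control patient.

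The same section has the DSMB judge attribution to ECCO2R afterwards and provides for SAEs that are not study-related. That fits the first reading better but does not settle it.

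**The case against.** The strongest reply is that much of the harm in controls is still measured. Septic shock, severe hypoxemia, prolonged ventilation and death are components of the primary outcome, analysed by intention to treat and also separately. Sepsis, tracheostomy and intubation are compared between arms as secondary endpoints. A fatal or hospitalization-prolonging infection can also be an SAE under the first limb. This stands. A reader might infer that harm prevented by avoiding intubation cannot be seen at all, and the article does not support that. What is lost is mainly the non-serious infections, renal events and thromboses in Group A.

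A reader might also infer that both adverse events and SAEs are near zero in Group A by construction. That goes too far. Six clinical items carry no device condition. For SAEs, relatedness may bind only the second limb, and even where it binds both, the relation is to enrolment and not to ECCO2R. Control events are open to under-reporting but are not excluded.

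Finally, the article does not say that each item will be tested alone, so the infection example illustrates scale and does not reproduce a planned test. An overall event rate could include the six unconditioned items in Group A. That softens the bias but does not remove it, because the other clinical items are still counted in one arm only.

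**Conclusion.** The concern holds for non-serious adverse events. Followed as written, the plan gives a between-arm test that cannot be read as a comparison of harm, because 13 of 19 items are unavailable to Group A and the rest sit under a device-related label. The item count rests on the text and on no crossover. The error rates rest on assumed risks and capture shares. With nothing counted in Group A, false rejection for a single item ranges from 32% at a 2% risk to nearly certain at 10% or more.

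For SAEs the finding is narrower: the definition is ambiguous, and on one of its two readings it is open to differential ascertainment in an unblinded trial.

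The primary outcome, its test and the sample size are untouched by this point. It affects a listed secondary outcome that carries one side of the benefit-harm balance the trial sets out to judge.

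**What to change.** 1. Define the clinical events (infection, renal, bleeding at any site, thromboembolic, neurologic, pneumothorax, hemodynamic, platelets and the remaining clinical items) with identical criteria in both arms, from randomization and over the same window, without reference to ECCO2R. Compare these by intention to treat.
2. Report mechanical and cannula events descriptively, in Group B only.
3. Stop using ECCO2R-related as the default label for non-serious events.
4. Define SAEs by seriousness alone, record relatedness as a separate field, and compare all-cause SAEs between arms. This removes the OR/AND ambiguity.

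The cost is a revision of the Safety section and the eCRF, and a little more event recording in Group A. No new procedures are needed. Trial status says that recruitment had not begun at the time of writing. The change is best made before it does, because events not collected in Group A may not be recoverable later.
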